#### 10.3.2.17 30-days follow up

- successful contact
- Recent hospitalization and, if applicable, reason for admission
- Death of the patient
- New-onset clinical complaints.

#### 10.3.2.18 90 days follow up

- Successful contact
- Recent hospitalization and, if applicable, reason for admission
- Death of the patient
- new clinical complaints

#### 10.3.2.19 Antimicrobial therapy since 1st positive blood culture until discharge/transfer.

- • Drug
- Application type
- Application duration

### 10.4 Data acquisition and processing

Data acquisition is performed either directly or retrospectively (after initial recording of data in a paper CRF) via web application on the servers of the ZKS of the University Hospital Jena into the study management software "OpenClinica®". The software complies with regulatory requirements (GCP, 21CFR Part11). The data are retrospectively collected via an encrypted data connection (HTTPS) in input masks via web browser or, if this is not possible primarily via a paper CRF by a trained study nurse of the Site Management Unit of the CSCC, in the study centers. To ensure pseudonymous data analysis, a unique patient identification number (SIC) is assigned to each patient.

Data management is performed using the same software. Verification of the accuracy of the data is performed by range, validity and consistency checks during data entry. Non-plausible or missing data are clarified by the SUPPORT study nurse on site with the responsible staff in the study centers. Every change to the data, e.g. due to the incorporation of answered

queries at the centers, is documented in the database via an automatic change tracking (audit trail). By using a hierarchical access concept based on user roles, unauthorized access to the study data is not possible.

Backups of electronic data on the University Hospital servers are performed on a regular basis. The data storage (servers) are located in a separate locked room to which only designated system administrators have access. The database containing patient contact information is secured for access in the same way as the database containing clinical patient data; storage is on two different servers for data protection reasons.

The microbiological findings data are recorded within the framework of the AlertsNet infrastructure (Electronic Blood Culture Registry, EBCR). This process is described in more detail below.

The microbiology laboratory that examines the blood cultures sent in creates a laboratory report for each blood culture and sends it back to the clinic concerned. The findings are also recorded in the AlertsNet EBCR. After this, a semi-automated data exchange begins, which in the case of clinically relevant positive findings provides for the request for documentation of clinical data on the patient concerned by fax to the clinical facility (see AlertsNet technical IT concept version 4.3). If *S. aureus* is detected, in addition to informing the sending hospital, a fax message is automatically generated for the SUPPORT study center. For data protection reasons, this fax only contains pseudonymized data - personal data are only transmitted from the study centers to the SUPPORT study center after the patient has given his/her consent. A patient pseudonym is automatically generated for each finding/database entry (SIC; see **Section 10.1**). In addition to the SIC and the time of reporting, the clinical study center receives the clear names by fax; the SUPPORT study center in Jena receives only the SIC by fax. Only when the SAB-positive patient has consented to study participation does the SUPPORT study center receive his or her name and contact details for the planned telephone follow-up interview with a fax copy of the consent form (see study procedure in Section 7.1).

The transmission of personal data takes place exclusively via https, VPN connections or by fax.

## 10.5 Study documents and their storage (archiving)

The relevant study documents according to ICH-GCP are compiled and maintained in the central study folder (Trial Master File / TMF) in the study center and kept during the course of the study. The TMF as well as the Investigator Site File (ISF) are prepared by the SUPPORT study nurse together with the project management based on the applicable Standard Operating Procedures (SOPs) of the University Hospital Jena.

The investigator folders are handed over to the staff responsible for the study at the study centers during the initial visits. The study centers are responsible for maintaining them during the course of the study and for archiving them. The SUPPORT study nurse at the study center will check them at regular intervals and especially before study completion to ensure that they are up to date and complete. She will also inform the study teams before study completion to archive the study documents according to the applicable guidelines.

The archiving of the Central Study Folder (TMF) takes place at Jena University Hospital, taking into account the applicable SOPs. The preparation for its archiving is organized by the project management together with the SUPPORT study nurse. The archiving period is at least ten years after preparation of the final report. Study documents shall be retained in accordance with the archiving period applicable to the study centers, but not less than ten years. The study site or the investigator-in-charge must take precautions that prevent the accidental or premature destruction of these documents.

## 705 10.6 Privacy

706 As part of the study, it is necessary to collect and process personal data from the study  
707 participants (e.g., full name, initials of first and last name, date of birth, address) and data on  
708 treatment and the course of the disease (e.g., medical findings, types of treatment,  
709 prescribed medication). These data are collected at the study centers and stored  
710 electronically in pseudonymized form (i.e., without direct reference to the patient's name)  
711 using a patient identification number. The data will then be extracted at the centers by the  
712 SUPPORT study nurse and entered into the CRF, transmitted to the study center, reviewed  
713 and analyzed. In the event of withdrawal of consent to the study by the patient, including  
714 further data collection, no further data will be collected from the date of withdrawal. The data  
715 collected so far will continue to be used and evaluated within the study. If a patient only  
716 discontinues the study treatment, the data required for the study can continue to be collected  
717 and used.

## 718 11 Quality assurance

### 719 11.1 Standardization

720 The study management prepares a study manual describing the study-specific procedures,  
721 time windows and responsibilities ("Working Instructions") for the staff involved in the study  
722 implementation. This is made available to the study centers when the study is initiated (initial  
723 visit to the center); training on the use of the documents is also provided by the SUPPORT  
724 study nurse at the study center.

### 725 11.2 Control of the study process and data quality

726 The SUPPORT study nurse visits the participating study centers at appropriate intervals and  
727 randomly checks compliance with the requirements of the study protocol and the applicable  
728 guidelines (GCP). In this context, she checks in particular the study folder for up-to-dateness  
729 and completeness of the essential study documents and the documentation on patient  
730 screening and recruitment.

731 The SUPPORT study nurse at the study center enters the study data into the electronic  
732 database during her regular center visits. She is supported by the study teams in the clinics  
733 with regard to access to the source data of the study patients.

### 734 11.3 Monitoring data

735 Independent monitoring by the Center for Clinical Studies of the University Hospital Jena is  
736 not planned. Compliance with the study protocol and applicable guidelines (GCP) is regularly  
737 and randomly checked by the SUPPORT study nurse of the study center (see **paragraph**  
738 **11.2**).

### 739 11.4 Audits

740 The central quality management of the Jena University Hospital, the project and quality  
741 manager and/or the study coordinator of the CSCC may perform internal audits to check the  
742 process, documentation and completion of the study according to the study protocol and  
743 applicable guidelines (Declaration of Helsinki, GCP).

## 12 Ethical concerns, legal and administrative regulations

### 12.1 Declaration of Helsinki and Good Clinical Practice

The study will be conducted in accordance with the ethical principles originating in the Declaration of Helsinki (28). The current version of the Declaration will be observed. The recommendations of Good Clinical Practice ([http://www.dgrw-online.de/files/leitlinien\\_gcp\\_korrektur\\_2002\\_deutsche\\_version.pdf](http://www.dgrw-online.de/files/leitlinien_gcp_korrektur_2002_deutsche_version.pdf)) valid since 17.1.1997, will be taken into account as far as applicable for SUPPORT.

### 12.2 Ethics Committees

The study protocol, together with the other required documents, will be submitted to the responsible lead ethics committee (Ethics Committee of Jena University Hospital) with a request for evaluation and subsequently to the Ethics Committee of the Thuringian Medical Association (LÄK). The study can only begin after a positive evaluation without conditions by both ethics committees.

The ISFs of the participating investigational sites will each receive a copy of the approving evaluations of the ethics committees.

### 12.3 Subsequent changes

The study protocol must be adhered to. Changes or additions to the study protocol can only be initiated and authorized by the study management. The lead ethics committee and the ethics committees of the participating study centers will be informed of any changes to the study protocol. If necessary, the approving evaluation will be obtained again. Changes requiring evaluation may not be implemented before the decision of the ethics committee.

Changes to the study that have been approved by the Ethics Committee that are appropriate,

- have an impact on the safety of the persons concerned,
- Additional data collection or analysis that requires a change in patient information and/or consent,
- Influence the interpretation of the scientific documents on which the study is based or the scientific validity of the study results,
- Substantially change the way the study is managed or conducted,

may only be made if these changes have been approved by the ethics committees.

### 12.4 Legal regulations

The planned study is not a study according to the German Drug Law, Medical Devices Law, X-Ray Ordinance or Radiation Protection Ordinance.

### 12.5 Patient Insurance

The conclusion of a separate patient insurance is not necessary, since no study-related invasive measures are performed on the patient.

## 12.6 Registration

The study is to be registered in the following public study registers: German Clinical Trials Register (DRKS). The study director is responsible for the registration in the registry and the maintenance of the registry data.

## 12.7 Funding

The study is funded by the German Federal Ministry of Education and Research (BMBF), FKZ 01EO1502, as part of the second funding period of the Integrated Research and Treatment Center (IFB) "Sepsis and Sepsis Consequences" (CSCC 2.0) at Jena University Hospital. Further external funding is not planned for the study.

## 12.8 Final report and publication

In preparing the final report and publication, the standards of the CONSORT Statement (<http://www.consort-statement.org>), the SQUIRE Statement (<http://www.squire-statement.org>) will be considered, as well as the guidelines for authors in medical journals as recommended by JAMA (<http://jama.jamanetwork.com/public/instructionsforauthors.aspx>).

For publications, authors are required to refer to the study as follows:

*University Hospital Jena, Integrated Research and Treatment Center "Sepsis and Sepsis Consequences (CSCC 2.0)". This work was funded by the German Federal Ministry of Education and Research (BMBF), FKZ 01EO1502.*

respectively

*Jena University Hospital, Integrated Research and Treatment Center - Center for Sepsis Control and Care (CSCC 2.0). This work was supported by the Federal Ministry of Education and Research (BMBF), Germany, FKZ 01EO1502.*

*Abstracts that can be cited must refer to the CSCC and the sponsor in the same way. In addition, the logo of the CSCC and the BMBF must be used on posters. The publication of the study results is independent of the results.*

## 14.2 Data protection aspects

Data protection aspects of the flow chart of the SUPPORT study (see Technical IT Concept Version 4.3 AlertsNet, vote of the Thuringian Commissioner for Data Protection and Freedom of Information (TLfDI) dated April 10, 2015 (AZ: 278-7/2014.42)).

[figure not shown]

## 25 1.1 Additions to the recording of a SAB case

26 In addition to the procedure for automated reporting of a *Staphylococcus aureus*-positive  
 27 microbiological blood culture finding via the AlertsNet infrastructure (Electronic Blood Culture  
 28 Registry, EBCR) to the SUPPORT team as specified in study protocol version 1.07 dated  
 29 May 18, 2016, the report can also be made by telephone or fax by a member of the  
 30 microbiology laboratory staff. If necessary, this allows for faster processing of the SAB  
 31 findings message or earlier consultation, since findings are only transmitted via the EBCR at  
 32 24-hour intervals. In addition, at study sites where connection to AlertsNet is delayed,  
 33 SUPPORT study enrollment can be initiated without being tied to the EBCR.

34 As a rule, the message about the presence of a SAB case in a participating clinical institution  
 35 is transmitted to the SUPPORT team before obtaining informed consent from the attending  
 36 physician. In this case, no identifying information is to be forwarded, i.e., in a transmission of  
 37 the microbiology report by fax, this data is to be blacked out. In individual facilities, consent to  
 38 study participation may have already been obtained by early contact of the laboratory with  
 39 the informing physician before the SUPPORT team was informed or an automated receipt of  
 40 findings via the EBCR took place.

41 Since, in the case of premature transmission of findings, no sequential number (case code,  
 42 SIC) can be generated automatically for the procedure, or if a connection to the AlertsNet  
 43 EBCR is not yet available, an SIC is assigned manually, which can subsequently and after  
 44 import of the findings message into the AlertsNet EBCR be matched with the then  
 45 automatically generated SIC.

46 All further steps, beginning with the study center contacting the study physician at the clinical  
 47 facility to obtain informed consent (if not already obtained), will follow the study protocol.

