## 5 Participating study centers

This study will include at least 15 of the up to 39 hospitals participating in AlertsNet 2.0 and a total number of 500 patients. Participating hospitals will be randomized into 2 groups with 2 sequences: A-B or B-A. Here, A represents the intervention and B the control group ("standard of care"). During the intervention, treating physicians at participating hospitals will receive unsolicited telephone consults recommending an evidence-based set of interventions to treat SAB (11).

The condition for participation here is that the laboratory to which a hospital sends its microbiological samples is connected to AlertsNet2.0. With regard to the IT concept, reference is made to the AlertsNet2.0 application.

Qualification of the participating centers or treating physicians beyond routine clinical work is not necessary. The telephone consultation is carried out by a clinical infectiologist or a physician with sufficient infectiological experience. There is no minimum number of patients to be included. The change of the groups takes place individually for each center after inclusion of the first 17 patients or after 12 months at the latest.

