## 5.2 Conditions for participation in the study

A condition for a hospital's participation in the study is the hospital's connection to the AlertsNet platform, which allows the information about the presence of an *S. aureus-positive* blood culture to be sent directly to the SUPPORT study center. There are no restrictions regarding the size of the hospital or the patients treated. The responsibilities of the study centers are specified in cooperation agreements.

Patients participating in the study must meet the inclusion criteria stated in **Section 6.1**. No exclusion criterion must be present (see **Section 6.2**).

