## 7 Course of studies

### 7.1 Detailed study process

Information about a microbiological blood culture result *positive* for *S. aureus* is automatically reported to the SUPPORT team via the AlertsNet infrastructure (Electronic Blood Culture Registry, EBCR). However, data management is done separately. The system sends a fax to the treating hospital with the patient's clinical name, -year of birth, *subject identification code* (SIC) and microbiological findings. The study center at the UKJ, which is informed at the same time, does not receive any clear name information but only the information of a SAB detection in a specific institution and the automatically generated case code (SIC). The study center contacts the study physician at the clinical institution and, based on the relevant positive microbiological findings and using the SIC, asks for the patient to be included in the study. If the patient agrees to participate in the study after being informed by the study physician, the signed consent form is faxed to the study center. Only with this fax does the study center thus receive clear name information on the SAB-positive patient. Thereupon, for patients of the intervention arm, the telephone consultation with the treating physician is performed and subsequently the consultation is confirmed by fax (incl. therapy proposal). For patients in the control group (no infectious disease consultation), the two aforementioned steps are omitted. After inclusion in the study, only the informed consent form is faxed to the study center. A consultation is not performed for these patients.

The SUPPORT study nurse documents the data of the study patients pseudonymously in the CRF as soon as possible during her on-site visits. After 30 and after 90 days, a follow-up call is made to the patients by the study center. The contact details for this are recorded separately in the consent form (**Figure** and **Section 14.2**).

[figure not shown]

\*EBCR: Electronic Blood Culture Registry

325

326 **Figure:** Flow chart for the SUPPORT study.

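### Addendum 1.1 lets laboratory staff report cases by telephone or fax at their discretion, with no rule that reporting be the same in intervention and control phases; use that follows the arm could mask a benefit

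*Protocol*

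**What the plan says.** Protocol section 5.2 sets the entry condition for hospitals: "A condition for a hospital's participation in the study is the hospital's connection to the AlertsNet platform". Under section 7.1 a positive culture "is automatically reported to the SUPPORT team via the AlertsNet infrastructure".

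Addendum 1.1 changes this in two ways.

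- **A second route.** In addition to the automatic report, "the report can also be made by telephone or fax by a member of the" microbiology laboratory staff. Use is discretionary and has two stated purposes: "microbiology laboratory staff. If necessary, this allows for faster processing of the SAB" and then "findings message or earlier consultation, since findings are only transmitted via the EBCR at" 24-hour intervals. Faster processing applies in both arms. Earlier consultation applies only when a consult will follow.
- **Enrolment without the EBCR.** This is allowed "at study sites where connection to AlertsNet is delayed": there, "SUPPORT study enrollment can be initiated without being tied to the EBCR".

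The addendum also notes that in some facilities early contact between laboratory and physician may already have produced consent before the study team hears of the case.

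Other relevant provisions:

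- Section 5: "Participating hospitals will be randomized into 2 groups with 2 sequences: A-B or B-A". Section 4.2 says study physicians cannot be blinded.
- Section 9.1 counts 30-day mortality from SAB diagnosis. Section 6.1 makes written consent a condition of inclusion.
- The CRF items in section 10.3.2 include date and time of inclusion and date of blood culture collection. They include neither the route nor the time of notification.

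**The concern.** A cluster cross-over removes stable differences between hospitals, provided the same kinds of cases are enrolled in a hospital's two phases. Here enrolment comes after the event that starts the mortality clock. A patient who dies between diagnosis and consent is not in the trial, so the speed and completeness of notification help decide which early deaths are counted.

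The text allows notification to depend on the arm. The manual route is optional, one of its purposes exists only in intervention phases, and laboratories speak to physicians who know the phase. If staff telephone more readily when a consult will follow, two things can happen:

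- At connected sites, cases in intervention phases are notified up to about 24 hours sooner.
- At unconnected sites, they may also be notified more completely.

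Both admit early deaths in intervention phases that control phases miss. Observed mortality under intervention rises relative to control, against the direction the superiority trial is looking for. The selection occurs before eligibility and consent, so adjusting for baseline factors among enrolled patients cannot be relied on to undo it.

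**Working it through.** **The plan's own figure.** Section 9.3: 15 centres × 30 patients = 450, or 225 per arm. Simple two-proportion power at two-sided 5% is 99.99% for 0.50 vs 0.25 and 99.2% for 0.70 vs 0.50. The stated power above 80% reproduces and does not depend on the reporting route.

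**Does a route change between phases bias the comparison?** Let d be a hospital's phase 1 minus phase 2 mortality. The period-adjusted effect is e = (mean d in A-B − mean d in B-A)/2. Let δ be the mortality difference due to route (assumed; the documents give none).

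- All hospitals manual in phase 1, EBCR in phase 2: shift = (δ − δ)/2 = 0.
- 5 of 15 hospitals change, independently of sequence: expected shift = (δ/3 − δ/3)/2 = 0.
- By chance, all 5 fall among 8 A-B hospitals: shift = (5δ/8)/2 = 0.3125δ, i.e. 0.9, 1.6 or 2.5 points for δ = 3, 5 or 8.
- Manual route in intervention phases only: shift = (δ − (−δ))/2 = δ, in full.

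**Null simulation.** Assumptions: 15 hospitals split 8:7, 15 patients per phase, 25% mortality in both arms (the in-hospital figure in section 1.3), between-hospital SD 0.3 on the logit scale. Analysis: cluster-level t test on 13 df, standing in for the GLMM. There were 8,000 runs per scenario, so the Monte Carlo standard error at 5% is √(0.05 × 0.95/8000) = 0.24 points.

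| Scenario | δ = 3 | δ = 5 | δ = 8 |
|---|---|---|---|
| All hospitals, phase 1 only | 4.4% | 5.2% | 5.3% |
| 5 random hospitals, phase 1 only | 5.6% | 4.7% | 4.7% |
| Intervention phases only | 10.3% | 19.5% | 41.5% |

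**What would produce such a δ?**

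*Completeness (unconnected sites).* Observed mortality = m·r_d/(m·r_d + (1 − m)·r_s), where r_d and r_s are the shares of future deaths and of survivors reported. Take r_s = 0.95 (assumed).

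- m = 0.25, r_d = 0.80: 0.200/0.9125 = 21.9% (−3.1 points)
- m = 0.25, r_d = 0.70: 0.175/0.8875 = 19.7% (−5.3 points)
- m = 0.50 (lower planning value for control, section 9.3), r_d = 0.80: 0.400/0.875 = 45.7% (−4.3 points)
- m = 0.50, r_d = 0.70: 0.350/0.825 = 42.4% (−7.6 points)

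A second null simulation used logistic regression with hospital and period terms (800 runs, Monte Carlo standard error 0.8 points). With r_d = 0.70 and r_s = 0.95 in the control phases of 5 hospitals, the mean odds ratio was 1.11 with 9.5% rejections. With no reporting difference, rejections were 5.4%. When the change followed period only, in 5 hospitals, they were near 6%.

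*Timing (connected sites).* If a fraction f of all patients die in the interval gained by the telephone report, control phases observe (m − f)/(1 − f). Solving for a shift δ gives f = δ/(1 − m + δ). At m = 0.25:

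- 3 points: f = 0.03/0.78 = 3.8%, or 15% of the deaths
- 5 points: f = 0.05/0.80 = 6.3%, or 25%
- 8 points: f = 0.08/0.83 = 9.6%, or 39%

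This also assumes that every intervention-phase case, and no control-phase case, is telephoned. Large shifts from timing alone would need a large share of deaths within about a day.

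**Effect on a real benefit.** Section 2.3 cites 27% vs 13%. Simple two-proportion power with 225 per arm is 96%. If arm-linked reporting narrows the gap to 27% vs 16%, 18% or 21% (δ = 3, 5, 8), power falls to 81%, 63% or 32%.

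**The case against.** A reader might infer that a change of route between a hospital's two phases itself shifts the comparison, for example where a late-connecting site starts on telephone reports and ends on automatic ones. The documents do not support this. Sequence is randomised, nothing links connection date to sequence, and section 9.5 names period effects. Only chance imbalance between sequences remains.

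A reader might also apply incomplete reporting in control phases to all 15 hospitals, which gives an odds ratio of 1.38 and 28% rejections. That conflicts with the addendum, which makes the manual report an addition. At connected sites the EBCR still reports positive cultures in both phases, so mainly timing changes. Incomplete case-finding is a concern only at unconnected sites.

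Three further points have weight.

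- **Motive.** Faster processing is phase-neutral, and the documents do not say whether laboratory staff know the current phase. Arm-linked use is therefore a possibility. It stays open because the physicians they contact do know.
- **Direction.** The likely bias works against the intervention, so it does not threaten a false claim of benefit. It does threaten a missed one.
- **Existing safeguards.** The screening log, SIC matching after import, the nurse's checks (section 11.2) and the culture and inclusion dates all help. Matching covers only reported cases, however. The log depends on the study centre learning of the case, and the checks cover screening documents, not the laboratory's list. Section 10.4 puts a time of reporting on the automatic fax, but it is not a listed CRF item.

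Whether the model has cluster-by-period terms cannot be seen from section 9.5, so nothing here rests on their absence.

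**Conclusion.** The point holds in a limited form. Addendum 1.1 leaves the reporting route to discretion, gives it a purpose that exists in one arm only, and sets no requirement of equal reporting across phases. Reporting that tracks the arm would bias the primary comparison by the full route difference, probably towards masking a benefit. Changes that track calendar time or connection date cancel on average.

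The size is conditional. At an assumed 3 to 8 points, false rejection in a null trial rises from about 5% to between 10% and 41%, and power for the effect cited in section 2.3 drops from 96% to between 81% and 32%. The upper end would be hard to reach through timing alone. These figures assume that the link to arm is complete and acts in every hospital; partial use scales them down. The documents show neither that the link exists nor how large it is. The change is still worth making, because later analysis cannot recover notification data that were never captured.

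**What to change.** In addendum 1.1, with a cross-reference in section 7.1:

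1. Require laboratory staff to report *S. aureus*-positive cultures in the same way in both phases of a hospital, whatever the arm.
2. Add route and time of notification to the CRF items in section 10.3.2.
3. At sites that enrolled without the EBCR, compare the laboratory's list of positive cultures, or the later-imported EBCR list, with the screening log for each phase. Log unreported cases as *not notified*.
4. Report by arm the share of positive cultures notified and the time from culture to inclusion.

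The cost is addendum wording, two CRF fields, a list comparison at the affected sites using pseudonymised data, and slightly more work for laboratories and the study nurse. Sample size and the primary analysis are unchanged.
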